##### Executive Function

Measures of executive function will consist of a web-based modified flanker task, the Oral Trail Making Test (OTMT) parts A and B, and a verbal fluency (VF) test (animal naming). The modified flanker task includes a set of response inhibition tests to assess the ability of the participants to suppress responses that are inappropriate in a particular context [68,69]. In total, 3 types of stimuli—incongruent, congruent, and neutral—will be represented by arrowheads. In all sessions, the participants will be asked to complete 4 blocks: 1 practice block consisting of 30 mixed stimuli (10 experiments per flanker arrow type) to help familiarize the participants with the task, 2 blocks consisting of 100 trials (20 incongruent and 80 congruent flanker arrows [70]), and 1 block consisting of 100 trials (all neutral flanker arrows). The display duration of the flanker arrows will be 150 ms, and the intertrial interval duration (from a + sign to the next) will be 1500 ms (−100 to +100 ms). The participants will be asked to sit in a quiet room while directly facing their computing device. They will be instructed to keep their index fingers on the right and left arrow keys of their computer keyboard (to indicate the direction of the flanking arrow), look at a small white fixation cross in the middle of a black screen where the target stimuli will appear, and respond as quickly and accurately as possible. The task will take approximately 10 to 15 minutes to complete, and the participants will be able to take a break in between blocks if they wish. The OTMT is a neuropsychological test and can reflect a wide variety of cognitive processes [71-73]. The test consists of 2 conditions: condition A, in which the participants are instructed to count from 1 to 25, and condition B, in which the participants are instructed to count in an alternating numeric and alphabetic sequence (ie, 1-A-2-B). The goal of the test is for the participant to finish both parts as quickly as possible, and the time taken to complete the test will be used as the primary performance metric. The OTMT takes approximately 2 to 5 minutes to complete. VF is a widely used test of executive function in which the participants will be given 60 seconds to produce as many unique words as possible within a semantic category (ie, names of animals) [74,75]. The number of unique words will be the participant’s score on this task. Both the OTMT and VF will be administered in an oral format via phone or an audio- and videoconferencing platform with the guidance of a trained researcher.

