For the SJ task, the participants will be instructed to report, using the number *1* and *2* keys on their keyboard, whether they perceived the auditory and visual stimuli as occurring simultaneously (number *1* key) or not (number *2* key). A total of 10 trials will be presented in a randomized order for each SOA, and 6 practice trials will also be presented for a total of 76 trials. This task will take approximately 5 to 10 minutes to complete. The experimental design of the TOJ task will be identical to that of the SJ task with the exception of the task instructions. In this case, the participants will be asked to report, using the number *1* and *2* keys on their keyboard, whether they perceived the visual (number *1* key) or auditory (number *2* key) stimulus as appearing first.

For the RT task, the participants will be told that they will see a flash of light, hear a beep, or a combination of the 2, and they will be instructed to press the response button (space bar key) as soon as they detect any of the 3 experimental conditions. Each condition will be presented 50 times in a random order with 6 practice trials for a total of 156 trials. However, if a participant responds too quickly (<100 ms) or takes longer than 3 seconds to respond to a trial, that trial will be repeated. This task will take approximately 5 to 10 minutes to complete.

Both the multisensory integration and modified flanker tasks will be designed using PsychoPy (Open Science Tools Ltd) and distributed on the web using Pavlovia (Open Science Tools Ltd), wherein the participants will be provided with URLs to access the tasks. All instructions will be embedded within the tasks and will not require the presence of a researcher to be completed. However, a researcher will join the participants for the duration of the first session of these tasks to ensure that all inquiries and technical difficulties are resolved as soon as they arise. Furthermore, 1 to 2 members of the research team will check in with the participants every 2 weeks to answer any questions and ensure that they are following the protocol.

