#### Executive Function

Cognitive data from the OTMT (completion time [seconds] for parts A and B separately) and VF (the number of unique animal names) will be analyzed for within-participant and between-participant variables. For the modified flanker task, the participants’ mean RT and proportion error (1-accuracy) for each block of flanker responses will be obtained and further separated by congruence (congruent, incongruent, and neutral). Incorrect responses, responses that occurred 1000 ms after stimulus onset, and double responses for a single stimulus will be considered as errors and excluded from the analysis. The rate of no response and gender will be included as covariates.

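### The flanker response rule names the flanking arrow instead of the central target, and no scoring key is stated, so as written the instructed key is reversed on the 40 incongruent trials per session

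*Protocol article*

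**What the plan says.** The task is described in the protocol article under Outcomes and Measures, Executive Function. Its purpose is given as "response inhibition tests to assess the ability of the participants to suppress responses that are inappropriate in a particular context". Participants are to "look at a small white fixation cross in the middle of a black screen where the target stimuli will appear", and they respond with the right and "left arrow keys of their computer keyboard (to indicate the direction of the flanking arrow". The article adds that "3 types of stimuli—incongruent, congruent, and neutral—will be represented by arrowheads".

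Each session has a practice block of 30 mixed trials, two blocks of 100 trials with 20 incongruent and 80 congruent each, and one block of 100 neutral trials.

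Under Statistical Analysis Plan, Executive Function, the outcomes are mean response time and proportion of errors by block and congruence. There, "Incorrect responses, responses that occurred 1000 ms after stimulus onset, and double responses for a single stimulus will be considered as errors" and are left out of the analysis. The direction that makes a response correct is not defined in either section.

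The Multisensory Integration section, in a paragraph that also covers the flanker task, says: "All instructions will be embedded within the tasks and will not require the presence of a researcher to be completed". A researcher joins for the first session, and team members check in every two weeks.

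**The concern.** In a flanker task that measures inhibition, the person answers to the target and suppresses the response prompted by the arrows beside it. The response rule in the article names those neighbouring arrows, while the same sentence places the target at the centre. On congruent trials both rules give the same key, so the conflict does not show. On incongruent trials they give opposite keys, and this is the condition that carries the inhibition contrast.

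The rule is stated, not left open, so this is not a detail deferred to a fuller document. The other keyboard tasks (simultaneity judgment, temporal-order judgment, response time) have response rules that fit their purpose.

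If the deployed text follows the article, incongruent accuracy and response time would be distorted for anyone who follows it literally. Flanker accuracy and response time also enter the exploratory correlations. The assessment protocol is meant to inform a larger trial, so the wording could be carried forward.

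**Working it through.** **Inputs (protocol article, Outcomes and Measures, Executive Function).** Mixed blocks: 2, each with 20 incongruent and 80 congruent trials. Neutral block: 100 trials. Practice: 30 trials. Interval between trials: 1500 ms.

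**Reproducing the article's count.** 20 + 80 = 100 trials per mixed block, as stated. Reading the 100 as per block is consistent with the stated task time: 30 + 200 + 100 = 330 trials, and 330 × 1.5 s = 495 s = 8.25 minutes, which fits 10 to 15 minutes once instructions and breaks are added.

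**Trials on which the two rules disagree.**
- Incongruent trials per session: 2 × 20 = 40.
- Share of mixed trials: 40 / 200 = 20%.
- Share of scored trials, practice excluded: 40 / (200 + 100) = 13.3%.
- Congruent trials, where both rules give the same key: 2 × 80 = 160 of 200.

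**Case A: literal responder, scored against the central target.** Let *a* be the assumed probability of pressing the key that the literal rule calls for. Congruent accuracy is *a*, incongruent accuracy is 1 − *a*, and mixed-block accuracy is (80*a* + 20(1 − *a*)) / 100.

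| *a* (assumed) | Congruent | Incongruent | Mixed block |
|---|---|---|---|
| 1.00 | 100% | 0% | 80% |
| 0.95 | 95% | 5% | 77% |
| 0.90 | 90% | 10% | 74% |

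Overall accuracy would look only moderately low, while the incongruent condition would be inverted. Because errors are excluded, 0 to 4 of the 40 incongruent response times would remain (40 × 0 to 40 × 0.10).

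**Effect on an arm mean, as an illustration.** If one person in an arm of 12 responded this way with perfect compliance, and would otherwise have had an incongruent error rate *b*, the arm's mean error rate would rise by (1 − *b*) / 12. That is 8.3 percentage points at *b* = 0 and 0.9 / 12 = 7.5 points at an assumed *b* of 10%. The article gives no basis for how many people, if any, would do so.

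**Case B: scored against the flanker.** Accuracy is not inverted. The central arrow becomes the competing stimulus, so the incongruent contrast measures something other than suppression of flankers.

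The article does not say which case applies.

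**The case against.** The strongest objection is that this is a slip of terminology. The article uses the term flanker arrow for the whole display: when it counts practice trials by type, when it gives the congruent and incongruent numbers, and when it gives the display duration. The fixation instruction and the stated purpose both point to a central target. The disputed words are in a parenthesis of a condensed article, and nothing says they are the on-screen text. There are also safeguards: a practice block in every session, a researcher throughout the first session, and fortnightly check-ins.

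Much of this stands. A slip is plausible, and any harm depends on task text and a scoring key that are not shown. It does not clear the wording, though. An incongruent display contains two directions, so if the term means the whole display, the response rule is undefined rather than right.

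A reader might go further in three ways that the article does not support:
- *That the task no longer measures response inhibition.* Even under the literal rule, a fixated central arrow pointing the other way would compete for the response. The contrast would be reversed or altered, not abolished.
- *That the 100 neutral trials are also affected, giving 140 of 300 (47%).* This needs neutral flankers without a left or right direction. The article says that all three types are shown as arrowheads and does not define neutral further.
- *That participants would switch rules between the supervised first session and later ones.* Nothing in the article indicates this.

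**Conclusion.** The point holds as an error of wording with a possible consequence for the data. The stated response rule conflicts with the central target in its own sentence and with the stated purpose, no other section corrects it, and the correct key is undefined. The supportable extent is 40 of 300 scored trials per session (13%), and only if the rule was deployed and followed literally. In that event, scoring against the target would leave incongruent accuracy near zero and almost no incongruent response times; scoring against the flanker would give a contrast that is not the intended one.

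The flanker task is one of three executive function instruments and a secondary outcome in a non-randomised pilot. The primary feasibility outcomes do not depend on it.

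**What to change.** - Reword the rule so that participants *indicate the direction of the central target arrow and ignore the flanking arrows*.
- State in the analysis section that correctness is scored against the central target.
- Check that the deployed on-screen text and scoring key match.
- Use the same instruction in both groups. The Results section reports 15 people enrolled in the experimental group by August 16, 2021, with control recruitment due to start in September 2021. A change made for controls alone would put a difference in instruction into the group comparison.
- If the experimental group worked to the wrong text, document this. As a sensitivity analysis, identify sessions with high congruent accuracy but incongruent accuracy far below the 50% expected by chance with two keys, and report results with and without them.

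If the program already uses the central arrow, the cost is a sentence or two in the protocol and a quick check. Otherwise it adds a correction to the task, a note of the deviation and a simple screen of data already collected.

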## Methods

### Study Design

This is a 6-week pilot study to examine the feasibility, acceptability, and usefulness of a co-designed VR exergame intervention among older adults as well as the feasibility of the study procedures and assessment protocol. A control group will be used to account for practice and exposure effects and will follow the same protocol as that described for the experimental group without exposure to the exergame; they will read 3 times a week for 15 to 20 minutes instead of engaging with our exergames. To maintain consistency between the control and experimental conditions, the same questionnaires and surveys will be completed by all the participants in both groups, except for the *perceived enjoyment* and *rate of perceived exertion (RPE)* scales, which will be completed only by the experimental group. Both qualitative and quantitative methods will be used to provide pilot data on potential outcomes of interest. Although this study will evaluate the feasibility of both the study intervention and study control arms, we will not randomize the participants. Participants in the intervention arm will be recruited first, followed by a wave of participants recruited to the control group. The study is based in Waterloo but will be carried out remotely, so participants from across Canada will be eligible.

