##### Automatic Data Logging System

*Seas The Day* includes a data logging system that allows for the capture of data related to game events and interactions inside the virtual environment during gameplay. In every session, the data logging system locally records data using a time series at 30 Hz combining game events, scores, achievements, and kinematic information from the VR equipment (controllers and headset). The data logging system records the following information: (1) tai chi (time to complete the activity and interactions with animals [when players were looking at them]), (2) rowing (boat speed, distance traveled, number of strokes [right or left], boat collisions, and interactions with the dolphin), and (3) fishing (number of fish caught, pulling out the fishing rod [number of repetitions], and RT after the fish is hooked). The kinematic information is captured through the inertial motor units embedded in the 2 VR controllers and the headset, recording 3-axis accelerometer information of the 3 points (head and right and left hand). Both game variables and kinematic information are locally stored in the headset and compressed in files of 15 MB.

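### Verbal fluency is animal naming and every stage of the game shows animals, so an acute gain in the exergame arm may partly be content cueing that the reading control cannot offset

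*Protocol article*

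**What the plan says.** All references are to the protocol article.

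- **The test.** Under Outcomes and Measures, Executive Function, the article states that "VF is a widely used test of executive function". Participants have 60 seconds to "produce as many unique words as possible within a semantic category (ie, names of animals". No other category is mentioned.
- **The score and its use.** In the Statistical Analysis Plan, "VF (the number of unique animal names) will be analyzed for within-participant and between-participant variables". Outcome Analyses compares groups on change across the 6 weeks and on change across a single bout of exergaming or reading.
- **The schedule.** Table 2 ticks VF at baseline, before and after in weeks 1, 3 and 5, and at follow-up.
- **The game content.** Automatic Data Logging System lists, for tai chi, "interactions with animals [when players were looking at them"; for rowing, "boat collisions, and interactions with the dolphin"; and for fishing, "number of fish caught, pulling out the fishing rod".
- **The control.** Study Design says that "A control group will be used to account for practice and exposure effects", and that this group follows the same protocol but reads and has no exposure to the game. The reading material is not specified.

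Strengths and Limitations covers the home setting, self-report and the small sample. It does not mention the overlap between test content and game content.

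**The concern.** The acute comparison is meant to show whether one bout of exergaming changes executive function. For VF, the game also shows members of the tested category between the before test and the after test, in one arm only. A participant who has just seen a dolphin and caught fish may name them more readily, with no change in executive function.

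The control group handles repetition of the same test, because both arms repeat it equally. It does not handle a cue that comes from the game itself. A larger sample would not help, because the effect would be a systematic shift rather than noise.

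What is at stake is how one secondary measure is read. An acute VF gain could be taken as an executive-function benefit. It could also enter the planned exploratory correlations, and it could feed the larger trial, since Sample Size says the pilot is meant to inform that trial's sample size calculation. The primary feasibility, usability and acceptability aims are not affected.

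**Working it through.** The plan gives no figure to reproduce: no formal sample size calculation was made and no VF variability is stated. The check is therefore mainly a comparison of sections, followed by an illustration on assumed values.

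**1. Number and timing of VF tests (Table 2).** Baseline 1 + (before and after) 2 × 3 weeks + follow-up 1 = 8 administrations, all with the same category. Three of the eight are in the after slot. The week assignment agrees with Outcome Analyses, which gives weeks 2, 4 and 6 for the sound-induced flash illusion, the task on the alternate weeks.

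**2. What lies between the before and after tests.** In the experimental arm, one game session of 15 to 20 minutes with animals in each of its three stages. In the control arm, 15 to 20 minutes of reading of unspecified content.

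**3. What the group contrast can remove.** Write the acute change in each arm as a sum:

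- exergame: practice + exercise effect + cueing
- reading: practice + any effect of reading
- difference: exercise effect − reading effect + cueing

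Practice cancels, as Study Design intends. Cueing does not, and nothing in the plan estimates it separately.

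**4. Whether the other executive-function tests share the problem.** The flanker task uses arrowheads, and the OTMT uses numbers and letters. Neither overlaps with the game content, so VF is the one affected.

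**5. Illustration of scale.** Inputs: n = 12 per group (the planned minimum) and 2-tailed t tests (Outcome Analyses). Assumed, because the document gives neither: alpha 0.05, an SD of VF change s of 3 to 5 words, and a pure cueing shift b of 1 to 3 words. No true executive-function effect is assumed. The noncentrality is b / (s × √(2/12)) with 2 × 12 − 2 = 22 degrees of freedom. For b = 2 and s = 4 it is 2 / (4 × 0.408) = 1.22. The probability of a significant group difference in change is then:

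| Cueing shift (words) | SD 3 | SD 4 | SD 5 |
|---|---|---|---|
| 1 | 12% | 9% | 8% |
| 2 | 35% | 22% | 16% |
| 3 | 65% | 42% | 29% |

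The nominal rate is 5%. The table shows what cueing would do if it occurred at these sizes. It is not evidence that it does.

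**The case against.** Several points on the other side stand.

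- **Cueing is possible, not shown.** A reader might infer that the VF contrasts are biased towards the exergame. The document does not support that. It names only a dolphin and fish, plus unspecified animals in tai chi, and gives no count. A cued name raises the score only if the participant would not have said it anyway. Nor is the net direction between arms fixed: the reading content is unknown, and reading is itself verbal exposure.
- **The interval is not stated.** VF need not follow the game at once. The flanker task (10 to 15 minutes), the OTMT (2 to 5) and the response time task (5 to 10) share the same time points, 17 to 30 minutes in total. Their order is not given, and VF needs a researcher on the phone or by video.
- **Six-week change is a weaker case.** A reader might extend the concern to baseline versus follow-up, since up to 3 × 6 = 18 sessions come before follow-up. But follow-up VF is not tied to a session, and by then both arms have already named animals seven times. Lasting cueing is harder to argue.
- **The larger trial may not be sized on VF.** VF is one of three instruments in one of five secondary domains. With 12 per group the standard error of a standardised difference is about √(2/12) = 0.41, and the article already asks for caution. A specific claim about how far a later trial would be mis-sized would rest wholly on assumed values.
- **A trimmed score can err the other way.** Within a fixed 60 seconds, cued names take up time. If those names then score nothing, the exergame arm may be penalised.

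These points limit the strength and reach of the concern. They do not remove it for acute VF: the overlap is in the text, it is confined to one arm, and nothing in the plan addresses it.

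**Conclusion.** The concern holds for the acute VF contrast in weeks 1, 3 and 5. With animal naming as the only category and animals in every game stage, an acute gain in the exergame arm cannot be separated from cueing of animals just seen, and the reading control cannot offset that cueing. It is weaker for baseline versus follow-up.

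The size is unknown. It depends on how many names the game cues, how long after play VF is given, and the SD of change, none of which the document states. The conclusion assumes only that the logged animals are visible to players, which the logging description supports. This is a modest point of interpretation about one secondary measure in a non-randomised pilot.

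**What to change.** **For this study**

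1. Keep the raw count of unique animal names as the VF outcome.
2. Where word lists or recordings were kept, add a sensitivity score that excludes a fixed list of animals shown in the game. Draw up the list from the game content, without reference to the results. Apply it identically in both arms and report both scores. The article does not say whether the words themselves are kept, so this should be confirmed, and retention secured for the control wave that starts in September 2021.
3. State in the report that acute VF change is not by itself evidence of an executive-function effect. Rest that conclusion on the flanker task and the OTMT, and do not use acute VF alone to size the larger trial.

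Changing the category now is of little use. The experimental wave is due to finish by September 2021, as the control wave begins, so a new category would break comparability between arms.

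**For the larger trial**

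Choose a fluency category that does not occur in the game.

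**Cost**

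One word list, one scoring rule and a little more scoring work. The trimmed score may over-correct for the reason given above, and it does not remove cueing of related animals that are not on the list. It should therefore be read beside the raw count and should not replace it.
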